### Study Period

The enrolment is planned to start from June 2020 and will last until the planned number of enrolled patients has been met.

### Outcomes

The association between the level of engagement, as evaluated by the PHE-s®, and the patient's rate of understanding during the diagnostic interview, will be assessed to evaluate whether the degree of clarity of the information provided by the doctor influences the level of patient engagement.

The association between the level of patient engagement is calculated with the PHE-s® and patient's estimated rate of understanding according to the interview and the adherence to proposed treatments (compliance).

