### Hypothesis

The hypothesis to be tested is that clarity of communication between the treating physician and the patient at the time of diagnosis, and the patient's level of understanding of the information received, influences a patient's engagement and compliance with the care process.

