### Aims

This study aims to (1) collect quantitative data about the level of PDAC patients engagement and their rate of understanding of the received information and (2) investigate the association between engagement and rate of understanding and of these two variables with the level of compliance.

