## Methods and Analysis

### Study Design

This will be a monocentric cohort study (observational, cross-sectional) on PDAC patients.

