### Description of the Intervention (Schedule of Visits)

The study requires (i) the completion of the scheduled outpatients visit with a gastroenterologist, surgeon, or oncologist with strong expertise in PDAC, (ii) the filling of the PHE-S® questionnaire by the patient to investigate the level of engagement, and (iii) the completion of a semistructured interview to assess the rate of understanding of the information received from the doctor.

In more detail:
The treating physician will inform the patient about the study before starting the outpatient visit and communicating information on PDAC diagnosis and planned treatments. The treating physician will also ask permission to the patient regarding the presence during the visit of an external observer (a Ph.D. student in philosophy of language and communication), who will take notes regarding the information provided and will record the audio of the visit if the patient gives further (optional) consent.After the visit, the external observer will ask the patient further written informed consent to use the data collected during the interview and to complete the study. Informed consent forms are presented at this stage rather than at a preliminary stage to avoid anticipating the diagnosis of PDAC, which the patient might not have yet received from the doctor.The patient will be asked to fill in the PHE-s® questionnaire, which takes ~10 min to be completed. PHE-s® is a standardized and validated tool to measure patients' psychological readiness to engage in patients with different medical disorders.The external observer will conduct a semistructured interview of ~30 min to ask the patient questions concerning the clarity of the communication he had received from the doctor and the type of language used, to record the rate of understanding of the information. This phase will ideally take place following the PHE-s® questionnaire, but the patient will be free to postpone it to another moment or day given the possible difficulties for the patient to face an interview immediately following the communication of the diagnosis. The interview will be conducted by an expert observer in the field of language and communication (a Ph.D. student in philosophy of language and communication). The object of the interview is the language used by the treating physician and its clarity for the patient.

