## Discussion

Active engagement of the patient to the therapeutic program has been shown to be an important factor not only to obtain improved compliance but also to improve the outcomes (13, 14).

Data on the communication between physicians and patients with PDAC are scanty, and patients' engagement has not been systematically evaluated in this context (15).

We hypothesize that the clarity of communication between the treating physician and the patient and the degree of comprehension by the patient, especially during the first phases of the cure, are associated with the level of engagement and consequently with the compliance of patients with PDAC.

If the present pilot study will support this initial hypothesis, further action to improve the clarity of the clinical communication will be promoted.

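### The Outcomes section promises to evaluate whether the doctor's clarity influences engagement, but the design supports only the association named in the Aims

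*Protocol article*

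**What the plan says.** The article states its purpose in two ways.

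- **Directional.** The Hypothesis section holds that clear communication, together with the patient's understanding, "influences a patient's engagement and compliance with the care process". The Outcomes section says that the association between the PHE-s and the rate of understanding "will be assessed to evaluate whether the degree of clarity of the information provided by the doctor influences the level of patient engagement".
- **Association only.** The Aims section sets out to "investigate the association between engagement and rate of understanding and of these two variables with the level of compliance".

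The design section reads: "This will be a monocentric cohort study (observational, cross-sectional) on PDAC patients". According to the schedule of visits, the study procedures with the patient begin once the consultation is over: "After the visit, the external observer will ask the patient further written informed consent to use the data collected during the interview". The patient then completes the PHE-s, described in these terms: "PHE-s® is a standardized and validated tool to measure patients' psychological readiness to engage". The understanding interview comes next: "This phase will ideally take place following the PHE-s® questionnaire". It may be put off to a later time or day. Only one PHE-s is described.

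The Variables section defines the rate of understanding by setting the items the patient correctly understood against the items the doctor conveyed. The Statistical Analysis section relates engagement to clarity, taken in quartiles, with a Pearson test. It also plans logistic regression with engagement as outcome and clarity plus patient and disease features as explanatory variables. The Discussion adds that, if the pilot supports the hypothesis, "further action to improve the clarity of the clinical communication will be promoted".

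**The concern.** The Outcomes section takes a variable measured on the patient, reads it as the doctor's clarity, and says its association with engagement will show influence in one direction. Three explanations would each produce a positive association:

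1. Clearer communication is better understood and raises engagement.
2. Patients who are readier to engage take in more of what they are told.
3. A third factor, such as education or distress, moves both.

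The article's own description of the PHE-s, as readiness to engage, leaves room for the second: readiness may be something the patient brings to the visit. The documents do not show that this happens, but nothing in the design excludes it.

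If the plan is followed as written, a significant result would be reported as evidence that clarity influences engagement. Efforts to change how doctors communicate could then rest on an association that has another cause.

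**Working it through.** The article gives no effect size, power or standard deviation, so there is no sample-size figure to reproduce. The check has two parts.

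**1. What would be needed to establish direction, and what is there**

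| Needed | In the article |
|---|---|
| Exposure assigned, or varied independently of the patient | Observational (Study Design) |
| Engagement known before the communication | One PHE-s, after the visit (schedule of visits) |
| Exposure that reflects the doctor and not the patient | Items understood against items conveyed (Variables) |
| Analysis that uses prior engagement | Pearson test, and regression without prior engagement (Statistical Analysis) |

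None of the four is met. The regression may reduce confounding by the features it includes. It cannot settle direction, because placing engagement on the outcome side is a choice of the model and not something the data show.

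**2. Does a significant Pearson test favour one explanation?**

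Inputs: n = 45 and n = 60 (Power Size Calculation section); two-sided 5% level (Statistical Analysis section); a true correlation of 0.4, which is an assumption. Let U be understanding, E engagement, C a common cause, and e, e₁, e₂ independent noise, all standard normal.

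- Understanding drives engagement: E = 0.4·U + √(1 − 0.4²)·e
- Engagement drives understanding: U = 0.4·E + √(1 − 0.4²)·e
- Common cause only: U = √0.4·C + √0.6·e₁ and E = √0.4·C + √0.6·e₂, so the correlation is √0.4 × √0.4 = 0.4

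The share of 20,000 simulated studies with p < 0.05 was:

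| Explanation | n = 45 | n = 60 |
|---|---|---|
| Understanding drives engagement | 0.798 | 0.894 |
| Engagement drives understanding | 0.792 | 0.897 |
| Common cause, no effect either way | 0.794 | 0.895 |

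The mean r was about 0.40 in every cell. The simulation standard error is about √(0.8 × 0.2 / 20,000) = 0.003 per cell, so the differences within each column are noise.

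For context, the smallest significant |r| is t/√(n − 2 + t²), with t the 97.5% point on n − 2 degrees of freedom. This gives 0.294 at n = 45 and 0.254 at n = 60.

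The simulation treats both variables as continuous, whereas the plan cuts clarity into quartiles. That does not matter here. All three structures give the same joint distribution of U and E (bivariate normal, correlation 0.4), so any analysis of these two variables alone, quartiles included, behaves identically under each.

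**The case against.** The case on the other side has several sound parts.

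- **Order of measurement.** A reader might infer that recording the PHE-s before the understanding interview reverses the order the hypothesis needs. The documents do not support this. The communication takes place at the visit, where the observer notes what is said, and so precedes the PHE-s; the interview only ascertains afterwards what was understood. Giving the PHE-s first also protects the engagement score from a half-hour conversation about the doctor's language. The order is not a fault.
- **No pre-visit value.** The schedule of visits explains that consent forms follow the visit so as not to anticipate the diagnosis. A baseline PHE-s is hard to obtain under that constraint. This excuses its absence but does not supply the missing information.
- **Mostly association language.** The Abstract, the Aims and the Discussion's restatement of the hypothesis all speak of association or relation, and a motivating hypothesis may be causal. That is fair, but the purpose given in the Outcomes section remains directional and conflicts with the Aims.
- **The Discussion.** A reader might take the sentence on further action as a decision rule. It is a soft closing statement about a pilot, and further action could include another study. It would still be better to say so.
- **Compliance.** Treatments are received after both measurements, so the direction problem does not apply equally to compliance.

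What stands is narrower: the engagement-understanding link is given a directional purpose that neither the data nor the analysis can serve.

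**Conclusion.** The point holds for the link between engagement and understanding. The directional purpose in the Outcomes section, and in the engagement half of the Hypothesis, goes beyond both the Aims and the design. The share of any observed correlation that is due to clarity acting on engagement cannot be estimated from this design, and a larger sample would not change that. The simulated figures rest on the assumed correlation of 0.4, but the equality across the three explanations does not depend on that value.

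The conclusion assumes that comprehension can be affected by what the patient brings to the visit. The documents neither show nor exclude this. It does not question the value of the pilot, the order of the questionnaires or the collection of the data. What should change is what the study says it may conclude.

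**What to change.** - **Outcomes:** replace the clause on influence with a statement that the association between the PHE-s and the rate of understanding will be estimated, as in the Aims. Add that direction cannot be inferred for this link, and that the rate of understanding reflects the patient as well as the doctor and so is not a pure measure of the doctor's clarity.
- **Hypothesis:** change *influences* to *is associated with* for engagement. Treat compliance in a separate clause, because it accrues later.
- **Discussion:** say that a positive result would be the basis for a study that tests a change in communication.

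A tempting addition is to repeat the PHE-s at follow-up and adjust for the score from the index visit. It is not recommended. The index score is taken after the communication, so adjusting for it would remove the immediate effect the hypothesis concerns. The article also fixes no follow-up contact at which to take the repeat.

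The cost is wording only: no measurement, analysis or sample size changes. The downside is that the study can claim less.

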### Description of the Intervention (Schedule of Visits)

The study requires (i) the completion of the scheduled outpatients visit with a gastroenterologist, surgeon, or oncologist with strong expertise in PDAC, (ii) the filling of the PHE-S® questionnaire by the patient to investigate the level of engagement, and (iii) the completion of a semistructured interview to assess the rate of understanding of the information received from the doctor.

In more detail:
The treating physician will inform the patient about the study before starting the outpatient visit and communicating information on PDAC diagnosis and planned treatments. The treating physician will also ask permission to the patient regarding the presence during the visit of an external observer (a Ph.D. student in philosophy of language and communication), who will take notes regarding the information provided and will record the audio of the visit if the patient gives further (optional) consent.After the visit, the external observer will ask the patient further written informed consent to use the data collected during the interview and to complete the study. Informed consent forms are presented at this stage rather than at a preliminary stage to avoid anticipating the diagnosis of PDAC, which the patient might not have yet received from the doctor.The patient will be asked to fill in the PHE-s® questionnaire, which takes ~10 min to be completed. PHE-s® is a standardized and validated tool to measure patients' psychological readiness to engage in patients with different medical disorders.The external observer will conduct a semistructured interview of ~30 min to ask the patient questions concerning the clarity of the communication he had received from the doctor and the type of language used, to record the rate of understanding of the information. This phase will ideally take place following the PHE-s® questionnaire, but the patient will be free to postpone it to another moment or day given the possible difficulties for the patient to face an interview immediately following the communication of the diagnosis. The interview will be conducted by an expert observer in the field of language and communication (a Ph.D. student in philosophy of language and communication). The object of the interview is the language used by the treating physician and its clarity for the patient.

All patients will then be treated and followed up normally in the context of the multidisciplinary team of the Pancreas Center that also include the aid of “navigator” and “research” nurses.

### The Medication of the Study

The study is observational, so a preplanned treatment is not considered.

### Statistical Analysis

Categorical variables will be compared using Fisher or chi-square tests and continuous variables using *t* test or Mann–Whitney tests, as appropriate. Subgroups with different levels of engagement will be compared for variables such as sex, age, education, geographic area, stage of disease, type of proposed treatment, and other available data. The PHE-s® questionnaire provides continuous data. The possible correlation of the level of engagement with the clarity of the received information that will be considered as a categorical variable divided in quartiles and with the compliance with treatments will be tested by a Pearson test. Two different univariate and multivariate logistic regression analyses will be run considering patient engagement and compliance as outcome variables and patients' and disease features and the clarity of communication as explanatory variables.

The “enter” method will be employed including all variables that had resulted to be significant at the univariate analysis. Tests of statistical significance and confidence intervals will be two-sided; a *p* < 0.05 will be considered to be statistically significant. A dedicated software (Medcalc 12.1, Belgium) will be employed.

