### Variables

The following variables will be recorded in a dedicated Case Report Form (CRF): age, sex, region of origin, educational level of the patient, habits such as smoking and alcohol intake as previously reported (12), date of the histological diagnosis of pancreatic adenocarcinoma, its stage, and the proposed treatment plan.

The level of patient engagement will be evaluated through the PHE-s® (see Appendix 1).

The rate of understanding of the information received from the patient by the doctor will be determined during a semistructured interview (see Appendix 2) by comparing the number of information conveyed by the doctor with the number of information received/correctly understood by the patient.

The compliance with treatments will be defined as the rate of treatments received compared to what was proposed and planned by the treating physicians and was considered possible by the medical team in light of patient's conditions and side effects.

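### The understanding measure is cut into quartiles, called categorical, and then correlated with engagement by a Pearson test: the description contradicts itself and the cut loses information for no stated reason

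*Protocol article*

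**What the plan says.** The Outcomes section of the protocol article lists this association first: "The association between the level of engagement, as evaluated by the PHE-s®, and the patient's rate of understanding during the diagnostic interview, will be assessed". It gives as the purpose to learn whether the clarity of what the doctor says influences engagement.

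The Variables section obtains the rate of understanding "by comparing the number of information conveyed by the doctor with the number of information received/correctly understood by the patient". That is a count set against a count, so it is numeric as collected.

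The Statistical Analysis section states that "The PHE-s® questionnaire provides continuous data". The next sentence begins "The possible correlation of the level of engagement with the clarity of the received information" and continues "that will be considered as a categorical variable divided in quartiles and with the compliance with treatments will be tested by a Pearson test". It gives no reason for the cut and no scores for the quartiles.

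The same section says "Categorical variables will be compared using Fisher or chi-square tests", with t or Mann–Whitney tests for continuous variables. It adds that "Tests of statistical significance and confidence intervals will be two-sided", at the 0.05 level. The Power Size Calculation section expects 45 to 60 patients on grounds of feasibility and gives no effect size or power.

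**The concern.** A Pearson correlation needs two numeric variables. One sentence declares a variable categorical and assigns it that coefficient, so the sentence cannot be followed literally. One analyst might score the quartiles 1 to 4 and correlate. A second might compare four groups. A third might read the test as Pearson's chi-square and cut engagement as well. These analyses answer different questions and can give different p values for the first-listed outcome.

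The cut is also avoidable, because the rate exists before it is divided. Dividing it discards the differences between patients within a quartile. The resulting coefficient is no longer the correlation between engagement and understanding. With 45 to 60 patients there is little information to spare, and the Discussion says that support for the hypothesis would lead to action on clinical communication.

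**Working it through.** **Inputs from the protocol article:** N = 45 to 60, two-sided alpha 0.05, continuous PHE-s, understanding collected as a rate and cut at quartiles. The article has no power or efficiency figure to reproduce.

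**Assumptions, not in the article:** quartiles scored 1, 2, 3, 4; a linear relation of engagement to the rate; a true correlation rho of 0.3 to 0.5 for illustration; a normal rate as the benchmark, then other shapes.

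**Step 1. Attenuation under normality.** The cut points are −0.674, 0 and 0.674, and the variance of the scores 1 to 4 is 1.25.

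corr(score, rate) = [φ(−0.674) + φ(0) + φ(0.674)] / √1.25 = (0.318 + 0.399 + 0.318) / 1.118 = 0.925

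Efficiency = 0.925² = 0.856, a loss of 14.4%. In effective patients: 45 × 0.856 = 38.5 and 60 × 0.856 = 51.4.

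**Step 2. Other shapes for the rate.** The squared correlation of rate and quartile score was simulated with 2,000,000 draws per shape:

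| Assumed shape | Efficiency | Loss |
|---|---|---|
| uniform | 0.937 | 6% |
| beta(2,2) | 0.912 | 9% |
| beta(5,2) | 0.863 | 14% |
| beta(8,2) | 0.833 | 17% |
| 10 items, each understood with probability 0.7 | 0.799 | 20% |
| beta(5,1) | 0.782 | 22% |

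**Step 3. Power under normality.** By the Fisher z approximation, power ≈ Φ(atanh(r)·√(N−3) − 1.960), with r = rho for the uncut rate and r = 0.925·rho for quartile scores.

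For rho = 0.4 and N = 45, uncut: 0.4236 × 6.481 − 1.960 = 0.785, power 0.784. With quartile scores, r = 0.370: 0.3886 × 6.481 − 1.960 = 0.558, power 0.712.

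| N | rho | Uncut | Quartile scores |
|---|---|---|---|
| 45 | 0.3 | 0.52 | 0.46 |
| 45 | 0.4 | 0.78 | 0.71 |
| 45 | 0.5 | 0.95 | 0.90 |
| 60 | 0.3 | 0.65 | 0.58 |
| 60 | 0.4 | 0.89 | 0.84 |
| 60 | 0.5 | 0.99 | 0.97 |

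Simulation (20,000 runs per setting) at rho 0.4 gives 0.80 against 0.72 at N = 45 and 0.90 against 0.84 at N = 60. The two methods agree within about two points.

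The correlation detectable with 80% power is tanh(2.802/√(N−3)), divided by 0.925 for quartile scores: 0.41 uncut and 0.44 cut at N = 45; 0.35 and 0.38 at N = 60.

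**Step 4. False positives.** With rho = 0, simulated rejection by Pearson on quartile scores is 5.2% (N = 45) and 4.9% (N = 60).

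**Step 5. Quartiles as true categories.** A four-group analysis of variance, which the article does not name, has simulated power at rho 0.4 of 0.54 against 0.80 uncut (N = 45) and 0.69 against 0.90 (N = 60).

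**Step 6. What each remedy recovers under normality, rho 0.4.** Simulated power for uncut Pearson, Spearman and quartile scores is 0.80, 0.74 and 0.72 at N = 45, and 0.90, 0.86 and 0.84 at N = 60. Spearman's asymptotic efficiency is 9/π² = 0.912, a loss of about 9%. It therefore gains only about 2 points over quartile scores.

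**The case against.** The strongest defence is that quartiles of a rate are ordered, so Pearson on scores 1 to 4 is a linear trend test. This stands. A reader might infer from the word categorical that the planned test is invalid or produces false positives. Under the scored reading it does neither, and step 4 shows error near 5%. Inapplicability holds only if the quartiles are taken strictly as categories.

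It can also be said that scoring and test details are commonly left to the full plan. That excuses silence about the scores. It does not excuse a sentence that states both a categorical variable and a Pearson correlation. Reading the test as Pearson's chi-square does not rescue it either: the sentence speaks of correlation, comes directly after the statement that PHE-s is continuous, and would then need engagement cut too.

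The Statistical Analysis section says clarity, whereas the Variables section says rate of understanding. Treating them as one variable is an inference from the Outcomes section, which links them, and should be labelled as such.

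The consequences are limited. The study is a declared pilot with no stated power, so no promised operating characteristic is broken. Logistic regression of engagement, with clarity among the explanatory variables, is also planned, so the Pearson test is not the only analysis of this association.

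Two further inferences are tempting: that compliance will pile up near 100%, making Pearson unsuitable there, and that ties will prevent quartiles being formed. The article gives no distribution for either variable, so neither is claimed here.

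**Conclusion.** The point holds at moderate severity. The planned test of the first-listed association is described in contradictory terms, and on the workable reading it discards information that the study already collects.

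The loss should be quoted as a range of about 6% to 22%. The 14% figure is only the benchmark for a normal rate, a linear relation and equally spaced scores. Nothing in the article fixes the shape of the rate or the true correlation, so the power figures are illustrations: at rho 0.4, a fall of about 7 to 8 points with 45 patients and 5 to 6 with 60.

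The direction of the error is towards missing an association. The documents do not support a claim that significant results would be untrustworthy on this account.

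**What to change.** State that the understanding rate is analysed uncut against PHE-s, name the coefficient and report it with a 95% confidence interval. State also that clarity in this analysis means the rate of understanding defined under Variables, if that is intended.

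Pearson on the uncut rate recovers the whole loss when the relation is linear. Spearman is an acceptable robust alternative for a bounded rate, but under normality it costs about 9% efficiency and so returns only about 2 power points. The choice should be made before the data are seen.

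Keep quartiles for a descriptive table. If a p value is wanted there, name an ordinal trend test with its scores, or a multi-group comparison.

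The cost is about two sentences in the Statistical Analysis section, with no new data and no change to recruitment.

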### Power Size Calculation

There have been no previous studies on the association between the patient's understanding rate and the level of engagement and the consequent level of compliance in patients with PDAC. This is, therefore, a pilot study, and power size cannot be calculated. Considering that at S. Raffaele Hospital, some 500 new PDAC patients are seen per year, with the established inclusion criteria, it is considered plausible that 45–60 patients will be enrolled in 3 months.

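### Logistic regression is prescribed for an engagement score that the protocol calls continuous; splitting it in two would cost at least about 36% of the information in the adjusted engagement analyses

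*Protocol article*

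**What the plan says.** The Statistical Analysis section of the protocol article describes the engagement measure directly: "The PHE-s® questionnaire provides continuous data". The next sentence uses it as a number, correlating engagement with the clarity of the information received (in quartiles) and "with the compliance with treatments will be tested by a Pearson test". The sentence after that sets out the modelling: "Two different univariate and multivariate logistic regression analyses will be run considering patient engagement and compliance as outcome variables". Patient features, disease features and clarity of communication are the explanatory variables.

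The Variables section gives the scale of the second outcome: "The compliance with treatments will be defined as the rate of treatments received compared to what was proposed and planned by the treating physicians", further limited to what the team judged possible for that patient.

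The only hint of grouped engagement is "Subgroups with different levels of engagement will be compared for variables such as sex, age, education". The article gives neither the number of these groups nor their boundaries. On size, the Power Size Calculation section says "it is considered plausible that 45–60 patients will be enrolled in 3 months" and states that no power calculation can be made.

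**The concern.** The stated scale of the engagement outcome and the model prescribed for it do not match. Within three consecutive sentences the score is called continuous, entered as a number in a Pearson test, and made the outcome of a model for categories. To run the logistic model the score must first be categorised, and a two-way split throws away the differences between patients on the same side of the cut.

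The logistic regressions are the only adjusted analyses in the study. They are the only place where the link between understanding and engagement is separated from stage, education, age and the like. With 45–60 patients there is little information to spare, and the odds ratio would also depend on where the cut falls.

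For compliance the problem is milder. A rate can be modelled on the logit scale as it stands, but the text does not say whether the rate or a dichotomised version of it is meant.

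**Working it through.** **The plan's own figure.** There is no power, effect size or standard deviation to reproduce. The 45–60 patients are a feasibility figure: 500 new patients a year gives 500/4 = 125 in three months, and 45/125 = 36%, 60/125 = 48%. The article gives no eligible fraction to test this against.

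**Inputs from the article.** n = 45 and 60; two-sided tests at 0.05 ("Tests of statistical significance and confidence intervals will be two-sided; a *p* < 0.05 will be considered to be statistically significant"); engagement on a continuous scale.

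**Assumptions, not in the article.** The engagement score is roughly normal. The true correlation r with one continuous explanatory variable is 0.3, 0.4 or 0.5. Detectable correlations are given at 80% power.

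**Step 1: information kept after a two-way split.** For a normal outcome cut at point c, with a proportion p below the cut and normal density φ, the efficiency relative to the uncut outcome is φ(c)² / [p(1 − p)].

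- Median split: 0.3989² / 0.25 = 0.637, a loss of 36%. Effective n: 45 × 0.637 = 28.6 and 60 × 0.637 = 38.2.
- 75/25 split: 0.3178² / 0.1875 = 0.539, a loss of 46%. Effective n: 24.2 and 32.3.
- 90/10 split: 0.1755² / 0.09 = 0.342, a loss of 66%. Effective n: 15.4 and 20.5.

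The median split is therefore the best case under normality.

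**Step 2: smallest correlation detectable with 80% power.** By Fisher's z, r = tanh[(1.960 + 0.842) / √(n − 3)].

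- Score kept continuous: tanh(2.802/√42) = 0.41 at n = 45; tanh(2.802/√57) = 0.36 at n = 60.
- Median split, using the effective n from step 1: about 0.50 and 0.44.

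**Step 3: check by simulation.** Bivariate normal data, 4,000 runs per cell. The Pearson test on the uncut score (equivalent to simple linear regression) is compared with a logistic likelihood-ratio test after a split.

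| n | r | Continuous | Median split | 75/25 split |
|---|---|---|---|---|
| 45 | 0.3 | 53% | 38% | 33% |
| 45 | 0.4 | 80% | 60% | 52% |
| 45 | 0.5 | 95% | 82% | 74% |
| 60 | 0.3 | 65% | 47% | 40% |
| 60 | 0.4 | 90% | 73% | 65% |
| 60 | 0.5 | 99% | 91% | 87% |

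At r = 0 the rejection rates were 4.7% (continuous), 5.6% (median) and 5.9% (75/25) at n = 45, and 4.7%, 5.0% and 5.7% at n = 60. The split analyses do not lose power by being conservative.

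**Step 4: compliance.** Steps 1 to 3 are not carried over. A rate of received over planned treatments is bounded and may cluster near 100%, so a calculation that assumes a normal outcome does not describe it.

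**The case against.** The strongest reply has four parts.

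*The main association is tested elsewhere.* The Pearson test already relates engagement to understanding and to compliance without splitting engagement. This stands. A reader might infer that the whole study forfeits a third of its information; it does not. The loss falls on the regressions only.

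*Logistic regression is not wrong for a rate.* This also stands. A reader might infer that both outcomes are defined as continuous and that neither logistic model can be fitted without a cut. Only the engagement score is called continuous. A binomial or fractional logit is itself a logistic model and uses the compliance rate directly. For compliance the form of the model is left unclear, but the model type does not contradict the outcome. Similarly, an ordinal logit would spare engagement a two-way split, but the article does not name one.

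*The cut-point may be fixed in a document not shown.* It may be in the full protocol, an analysis plan or the appendix with the questionnaire, and the mention of engagement subgroups suggests that some grouping was intended. A reader might infer that the cut would be picked once the data are seen; the article does not show that. A cut fixed in advance would still not recover the lost information.

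*It is a pilot with no power target.* True, and the correlations used above are assumptions. But a small sample is a reason to keep information, and the plan still applies a 0.05 threshold and adjusted models.

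Two further inferences are not supported. Counting all candidate covariates to argue that the adjusted model is overloaded ignores the stated rule that only variables significant in univariate analysis enter. And quartile coding of understanding is a separate question about a predictor; the regression sentence does not repeat it.

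**Conclusion.** The point holds for engagement and should be fixed. The prescribed model does not fit the scale that the same section gives to the outcome. A two-way split would cost at least about 36% of the information in the study's only adjusted analyses of engagement, leaving 45–60 patients worth about 29–38 or fewer. At n = 45 and an assumed r of 0.4, power drops from about 80% to about 60%. These figures rest on a roughly normal score, a two-way split and a single continuous explanatory variable. They are not figures from the article and do not describe the Pearson analysis.

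For compliance the conclusion is narrower: the text should say whether the logistic model is applied to the rate or to a dichotomised version of it. No size is put on this.

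**What to change.** In the Statistical Analysis section:

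- **Engagement:** replace logistic regression with multiple linear regression of the questionnaire score, with robust standard errors, and a rank-based or ordinal model as a check.
- **Compliance:** state that the rate itself is modelled, by a binomial model (treatments received out of those planned and considered possible) or a fractional logit, with robust standard errors.
- **Dichotomies:** if a split of either outcome is wanted for presentation, state the cut in the plan and label the analysis secondary.

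The cost is a change of wording and possibly a second package alongside the named software. The engagement result would be reported in score points rather than as an odds ratio. No extra patients or data are needed; the score is already collected, and the rate already requires the received and planned treatments.
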